**6.4.6 Visit 6 (Week 16  $\pm$ 1week); Visit 7 (Week 20  $\pm$ 1week) 【phone visit】**

- Check for discontinuation of the study
- Adjustment of basic medication
- Record past/ concomitant medication
- Supervise the recording of patient diary (including blood glucose self-monitoring, etc.)
- Record adverse events

**6.4.7 Visit 8 (Week 26  $\pm$ 1week) 【outpatient visit】**

- Check for discontinuation of the study
- Physical examination
- Collection/distribution of patient diary
- Adjustment of basic medication
- Counting/retrieval of investigational medication
- Dispensation of investigational medication
- Record past/ concomitant medication
- Evaluation of compliance
- MMTT test 0, 60, 120 min blood glucose (conduct at each study site); 0, 60, 120 min C-peptide (deliver to central laboratory)
- 25(OH)D test, gene analysis (deliver to the central laboratory)

- HbA1c, blood routine test, blood biochemical, blood electrolyte, urine pregnancy test, 24-hour urine calcium and phosphate
- 12-lead ECG
- BUS of urinary system
- Record adverse events

**6.4.8 Visit 9 (Week 30  $\pm$ 1week); Visit 10 (Week 34  $\pm$ 1week) 【phone visit】**

- Check for discontinuation of the study
- Adjustment of basic medication
- Record past/ concomitant medication
- Supervise the recording of patient diary (including blood glucose self-monitoring, etc.)
- Record adverse events

**6.4.9 Visit 11 (Week 38  $\pm$ 1week) 【outpatient visit】**

- Check for discontinuation of the study
- Physical examination
- Collection/distribution of patient diary
- Adjustment of basic medication
- Counting/retrieval of investigational medication
- Dispensation of investigational medication
- Record past/ concomitant medication
- Evaluation of compliance
- Record adverse events

#### **6.4.10 Visit 12 (Week 42 $\pm$ 1week); Visit 13 (Week 46 $\pm$ 1week) 【phone visit】**

- Check for discontinuation of the study
- Adjustment of basic medication
- Record past/ concomitant medication
- Supervise the recording of patient diary (including blood glucose self-monitoring, etc.)
- Record adverse events

#### **6.4.11 Visit 14 (Week 52 $\pm$ 1week) 【outpatient visit】**

- Check for discontinuation of the study
- Physical examination
- Collection/distribution of patient diary
- Adjustment of basic medication
- Counting/retrieval of investigational medication
- Dispensation of investigational medication
- Record past/ concomitant medication
- Evaluation of compliance
- MMTT test 0, 60, 120 min blood glucose (conduct at each study site); 0, 60, 120 min C-peptide (deliver to central laboratory)
- GADA, 25(OH)D test, gene analysis (deliver to the central laboratory)
- HbA1c, blood routine test, blood biochemical, blood electrolyte, urine pregnancy test, 24-hour urine calcium and phosphate
- 12-lead ECG

- BUS of urinary system

- Tests for complications

- Record adverse events

**6.4.12 Visit 15 (Week 56  $\pm$ 1week); Visit 16 (Week 60  $\pm$ 1week); Visit 17 (Week 64  $\pm$ 1week); Visit 18 (Week 68  $\pm$ 1week); Visit 19 (Week 72  $\pm$ 1week) 【phone visit】**

- Check for discontinuation of the study

- Adjustment of basic medication

- Record past/ concomitant medication

- Supervise the recording of patient diary (including blood glucose self-monitoring, etc.)

- Record adverse events

**6.4.13 Visit 20 (Week 78  $\pm$ 1week) 【outpatient visit】**

- Check for discontinuation of the study

- Physical examination

- Collection/distribution of patient diary

- Adjustment of basic medication

- Counting/retrieval of investigational medication

- Dispensation of investigational medication

- Record past/ concomitant medication

- Evaluation of compliance

- MMTT test 0, 60, 120 min blood glucose (conduct at each study site); 0, 60, 120 min C-peptide (deliver to central laboratory)

- 25(OH)D test, gene analysis (deliver to the central laboratory)
- HbA1c, blood routine test, blood biochemical, blood electrolyte, urine pregnancy test, 24-hour urine calcium and phosphate
- 12-lead ECG
- BUS of urinary system
- Record adverse events

**6.4.14 Visit 21 (Week 82  $\pm$ 1week); Visit 22 (Week 86  $\pm$ 1week); Visit 23 (Week 90  $\pm$ 1week); Visit 24 (Week 94  $\pm$ 1week); Visit 25 (Week 98  $\pm$ 1week) 【phone visit】**

- Check for discontinuation of the study
- Adjustment of basic medication
- Record past/ concomitant medication
- Supervise the recording of patient diary (including blood glucose self-monitoring, etc.)
- Record adverse events

**6.4.15 Visit 26 (Week 104  $\pm$ 1week)/Discontinuation Visit 【outpatient visit】**

- Physical examination
- Collection/distribution of patient diary
- Adjustment of basic medication
- Counting/retrieval of investigational medication
- Record past/ concomitant medication

- Evaluation of compliance
- MMTT test 0, 60, 120 min blood glucose (conduct at each study site); 0, 60, 120 min C-peptide (deliver to the central laboratory)
- GADA, 25(OH)D test, gene analysis (deliver to the central laboratory)
- HbA1C, blood routine test, blood biochemical, blood electrolyte, urine pregnancy test, 24-hour urine calcium and phosphate
- 12-lead ECG
- BUS of urinary system
- Tests for complications
- Record adverse events

Note: 1.The contents of the discontinuation visit are consistent with that of visit 26; 2.Metformin (and insulin); 3.Saxagliptin/VitD3 (Group A does not involve any dispensation, check or retrieval of investigational medication; 4. Blood biochemical test include: Lipid (TC, LDL-C, HDL-C, and TG), liver function (AST, ALT, TBIL, DBIL, and ALB), renal function (BUN, Cr, andUA); 5. Apply to women at child-bearing period; 6.Tests for complications include: ① macroangiopathy: 1) Color Doppler Ultrasound of carotid artery, vertebral artery, and lower extremities arteries, 2) ECG; ② microangiopathy: 1) retinopathy: fundus examination and photography, 2) diabetic nephropathy: a.UACR, b. calculate eGFR; ③ peripheral neuropathy: 1) electroneuromyography, 2) physical examination using the tools in the diabetic neuropathy screening kit; ④ osteoporosis: bone mineral density. (Will accept Color Doppler Ultrasound of artery, fundus examination and photography and electroneuromyography reports from Grade A Tertiary Hospitals within 6 months prior to screening; will accept BMD test results from Grade A Tertiary Hospitals within 12 months of randomization).

## **6.5 Screening Failure**

Participants who fail the screening refer to those who have signed the informed consent, but do not enter the randomization.

Subjects dropped out after randomization (refer to 6.6 Discontinuation of Study) will not be replaced by new subjects, and the subjects' numbers could not be used again. Subjects cannot be enrolled into the study again once dropped out.

Subjects who have signed the consent form but failed in the screening period before randomization, are allowed to go through screening again if inclusion or exclusion criteria has changed. In this case, subjects have to sign the new consent forms and be assigned to new randomization numbers.

## **6.6 Discontinuation of Study**

Patients may be discontinued from the study if any of the following situations occur:

- Voluntary discontinuation by the subject, revoking the informed consent;
- Safety reasons as judged by the investigator;
- Severe non-compliance to protocol as judged by the investigator;
- Incorrect enrollment, i.e. the patient does not meet the required inclusion/exclusion criteria;
- Patient lost to follow-up (as defined by, unable to reach the patient after 3 valid phone calls, fax or email, all contact should be documented in the patient's medical records);
- Pregnancy;

Investigators should record the reasons of discontinuation or drop-out subjects. Subjects need to go through relevant process and inspection of discontinuation (identical to the 26st follow-up). The random coding and research drugs of these subjects cannot be passed on to other subjects.

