## **4.4 Procedures for incorrectly enrolled or randomized subjects**

Subjects who fail to meet the inclusion or comply with exclusion criteria should not, under any circumstances, be enrolled or receive study medication. There are no exception

to this rule. When patients are incorrectly enrolled, procedures for discontinuation should be followed. When any following situation occurs, i.e. subjects do not meet the inclusion or comply with exclusion criteria, enrolled in error, fail to meet study requirements and incorrectly treated, or when subjects seriously violate the study protocol post initiation, relevant endocrinologists should inform the principle investigator as soon as possible.

Violation of the main inclusion criteria, e.g. non-LADA patients enrolled in error into the study group, relevant results should not be included in the FAS analysis. But subjects of any other incorrect registration or randomization can be included in the FAS analysis. At the same time, investigators will provide subjects with guidance on blood glucose control.

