### **Compliance evaluation of investigational medication:**

Evaluation of compliance should be based on the returned tablet count at each visit. The subjects will be asked to return all untaken investigational products and the empty packages of the taken medication.

Compliance evaluation of Saxagliptin:  $\text{actual dose taken/prescribed dose} * 100\%$

Compliance evaluation of vitamin D3:  $\text{actual dose taken/prescribed dose} * 100\%$

Participants judged to be non-compliant can continue the study if the participants understand the importance of taking their study medication as prescribed, and are willing

to comply according to prescription. If the subject continuously fail to comply, the investigator can decide whether or not to terminate participants from this study.

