### **8.1.2 Intensity of adverse events and management**

When filling out the adverse event table, the investigator will use mild, moderate, and severe to describe the intensity of adverse events. To harmonize standards, the intensity of events is ranked as follows.

- (1) Mild: The event does not interfere with the normal daily activity of the subject, and there is no need for symptomatic treatment and discontinuation of dosing.
- (2) Moderate: The event partly affects the subject's normal daily activity and requires symptomatic treatment or discontinuation of dosing.
- (3) Severe: The event obviously interferes with subject's normal daily activity and requires emergency treatment or immediate discontinuation of dosing.

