### **8.1.3 Treatment of adverse events**

Investigators should determine whether to suspend the clinical trial according to the severity of the event and provide the diagnosis and necessary treatment based on his/her clinical experience. All adverse events should be tracked for investigation, the process and the result of the treatment should be recorded in details until the situation is properly solved or the patient's condition is stable, abnormal test results must be followed until the figures are normal.

The relevant treatment on some particular adverse events, such as severe nausea and vomiting, hypoglycemia, hypercalcemia and vitamin D intoxication should refer to 8.4-8.7.

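### Sections 6.6 and 4.4 treat safety reasons, severe non-compliance and wrong enrolment only as grounds for leaving the study, and collect no C-peptide after exit, so week-104 primary values are lost avoidably

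*Protocol*

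**What the plan says.** All references are to the protocol.

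- **Section 6.6** begins "Patients may be discontinued from the study if any of the following situations occur". One list follows: consent withdrawal, safety reasons, severe non-compliance, incorrect enrolment, loss to follow-up and pregnancy. There is no category for a subject who stops study drug and remains in follow-up. Those who leave have an exit assessment identical to visit 26.
- **Section 6.4.15** confirms this: "The contents of the discontinuation visit are consistent with that of visit 26". C-peptide from the mixed-meal tolerance test (MMTT) is therefore taken once, when the subject leaves.
- **Section 6.5** adds "Subjects cannot be enrolled into the study again once dropped out".
- **Section 4.4** is directive: "When patients are incorrectly enrolled, procedures for discontinuation should be followed". It bars violators of the main inclusion criteria, such as non-LADA patients, from the FAS, and continues "But subjects of any other incorrect registration or randomization can be included in the FAS analysis".
- **Section 5.4** lets non-compliant subjects continue. If non-compliance persists, "the investigator can decide whether or not to terminate participants from this study".
- **Section 8.1.2** grades a moderate adverse event as one that "requires symptomatic treatment or discontinuation of dosing", with no mention of leaving. Section 8.6 holds vitamin D3 in hypercalcaemia, and 8.7 reduces it to 800 IU above 250 nmol/L, again without exit.
- **Section 8.1.3** says "Investigators should determine whether to suspend the clinical trial according to the severity of the event". Section 8.7 also speaks of suspending the study when vitamin D is withdrawn above 500 nmol/L. Neither says whether drug or participation stops.
- **Sections 9.3.1 and 9.4.1** analyse the week-104 change in fasting C-peptide by MMRM on the FAS, in the randomised groups.

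**The concern.** The primary analysis set follows the randomised groups, and section 9.3.1 describes intention-to-treat as based on assigned rather than received treatment. That comparison needs week-104 values from subjects who have stopped drug, as far as they will still attend. The discontinuation rules allow those values to go uncollected, and for wrongly enrolled subjects they direct it.

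A C-peptide value from an early exit visit is not a week-104 value. For a subject who has left, the MMRM must infer week 104 largely from subjects still on drug. If exits are drug-related, differ between arms, and benefit fades after stopping, the treatment effect is overstated. Section 9.4.1 promises models for drop-outs and protocol violations, but a model cannot supply measurements that were never taken. The visit schedule is fixed in the protocol, so a later analysis plan cannot repair this.

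**Working it through.** **1. Is any C-peptide collected after exit?**

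The exit visit is a single visit (6.4.15, 6.6). Follow-up beyond exit is described only for safety: unresolved adverse events in 8.1.4 and pregnancy outcomes in 8.9. No section schedules an MMTT after exit.

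**2. Who is sent out?**

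- Wrongly enrolled but FAS-eligible subjects: directed out by 4.4.
- Safety reasons and severe non-compliance: possible under 6.6, at the investigator's discretion.
- Drug changed or held without exit: covered in 5.4, 8.1.2, 8.6 and 8.7. None of these states that a subject who permanently stops drug keeps MMTT visits to week 104.

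**3. The plan's own figure (section 9.2)**

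Inputs: means 149.2 and 108.4, so delta = 40.8; SDs 84.5 and 52.8; two-sided alpha 0.025; power 90%.

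- Pooled SD = sqrt((84.5² + 52.8²)/2) = 70.46.
- n = 2[(u_alpha + u_beta)/(delta/sigma)]² + u_alpha²/4 = 74.02 + 1.26 = 75.28, rounded up to 76.
- 76/0.80 = 95, set to 100.

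The sample size reproduces and is not in dispute.

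**4. Possible overstatement from drug stops**

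The protocol gives no drug-stop rate. Assume that a share p of Group B permanently stops saxagliptin, that all of them are removed, and that their week-104 values are inferred as if on drug.

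Overstatement = 40.8 × p × (1 − share of benefit kept at week 104), in pmol/L:

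| p | none kept | half kept | all kept |
|---|---|---|---|
| 5% | 2.04 | 1.02 | 0 |
| 2% | 0.82 | 0.41 | 0 |

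None kept is the upper edge. If benefit accrues linearly and what was gained is kept, the share kept is stop week/104. At p = 5%, stops at weeks 26, 52 and 78 then give 1.53, 1.02 and 0.51.

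For scale, the standard error with 80 per arm is 70.46 × sqrt(2/80) = 11.14. The ceilings are 2.04/11.14 = 0.18 and 0.82/11.14 = 0.07 standard errors.

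The 20% drop-out allowance is not used as a bound on p. It also covers consent withdrawal and loss to follow-up, which a wording change cannot recover.

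**5. Power if off-drug subjects are kept**

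Group A receives no investigational drug, so only Group B gains retained off-drug subjects. Critical z at two-sided 0.025 = 2.241. With m off-drug subjects added to 80 on drug in B:

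- difference = 40.8 × (80 + m × share kept)/(80 + m)
- SE = 70.46 × sqrt(1/80 + 1/(80 + m))
- power = Phi(difference/SE − 2.241)

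| Group A | Group B | benefit kept | difference | SE | power |
|---|---|---|---|---|---|
| 80 | 80 on drug | – | 40.80 | 11.14 | 92.2% |
| 80 | 80 + 5 off | none | 38.40 | 10.97 | 89.6% |
| 80 | 80 + 5 off | half | 39.60 | 10.97 | 91.4% |
| 80 | 80 + 10 off | none | 36.27 | 10.83 | 86.6% |
| 80 | 80 + 10 off | half | 38.53 | 10.83 | 90.6% |

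**6. Visits**

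At a 5% stop rate in Groups B and C: 0.05 × 200 × 4 = 10 × 4 = 40 MMTTs at most. Planned post-baseline MMTTs: 300 × 4 = 1,200. Share: 40/1,200 = 3.3%. Wrongly enrolled subjects are not counted here, because the protocol gives no rate for them.

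**The case against.** The case against is strong on several points.

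- **Discretion.** A reader might infer that everyone who stops drug is removed. The text does not say so. Section 6.6 uses *may*, and 5.4, 8.1.2, 8.6 and 8.7 change or hold drug without exit. Only pregnancy (8.9) ties a drug stop to leaving. A subject who is not discontinued stays on the Table 1 schedule. This stands, so the drug-stop part is conditional. What remains is that 6.6 offers exit and no alternative, across 20-45 centres that may read it differently.
- **The FAS.** A reader might infer that 4.4 contradicts the FAS definition. It does not. The FAS asks for at least one post-baseline efficacy assessment, not a week-104 value; 4.4 only says such subjects *can* be included; and an MMRM uses partial data. Taking wrongly enrolled subjects off drug is also sound, since many exclusion criteria concern safety. But stopping drug does not require stopping measurement, and the missing week-104 values are avoidable.
- **Bias from wrong enrolment.** Eligibility is settled before randomisation, so errors should fall similarly across arms. None of the calculations shows a bias from this group.
- **Size.** Even the ceiling is 0.18 of a standard error, and it rests on an assumed rate and on the removal of every stopper. Section 1.3 describes saxagliptin tolerability as similar to placebo, which favours the low end.
- **Supporting text.** The bar on re-enrolment in 6.5 does not address follow-up measurements, and the suspension wording in 8.1.3 and 8.7 is loose rather than an instruction to exit permanently. Neither carries the point alone.
- **Dilution.** Keeping off-drug subjects can take power below 90%, as the table shows.

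**Conclusion.** The point holds as a gap in data collection. Section 6.6 provides only exit for safety reasons, severe non-compliance and incorrect enrolment; 4.4 directs that exit for subjects who may remain in the FAS; and nothing collects their C-peptide afterwards. For wrongly enrolled subjects the loss follows from the text. For drug stops it depends on the investigator.

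The size is unknown and probably small: 0 to 2.0 pmol/L of 40.8, assuming that 2-5% of Group B stop saxagliptin, that all of them are removed, and that the benefit kept at week 104 ranges from all to none. The bias is zero if stoppers keep all their benefit. The documents do not support a claim that the primary result is materially biased, and no LOCF bias and no power gain are claimed. This is a cheap improvement of low severity.

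**What to change.** In section 6.6, separate (a) permanent stop of saxagliptin and/or vitamin D3 from (b) withdrawal from the study. State that two groups stay on the remaining scheduled MMTT visits (weeks 26, 52, 78 and 104) unless they withdraw consent:

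- subjects who stop drug for safety or non-compliance;
- subjects randomised in error who remain FAS-eligible under 4.4, off study drug.

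Cross-refer from 4.4 and 5.4. Cross-refer also from 8.1.3 and 8.7, and say there whether drug or participation is suspended. The rules for when drug is stopped, the pregnancy procedure in 8.9 and the FAS exclusion of non-LADA subjects stay as they are.

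The cost is wording plus visits already in the schedule: at most 40 of 1,200 MMTTs at a 5% stop rate, and a further number, not known, for wrongly enrolled subjects. The statistical downside is dilution: in the worst case worked, power is 86.6%, against 92.2% for 80 per arm all on drug. Collecting the values forces no particular analysis, so an on-treatment analysis remains possible. Not collecting them removes the choice.

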## **7. STUDY ASSESSMENTS**

The investigator must ensure that all data are accurately, completely, and timely recorded in the outpatient medical record (or study medical record) and EDC according to the research protocol.

### **7.1 Efficacy assessments**

- C-peptide: they were tested in a central laboratory. Detection was carried out by chemiluminescence using a commercially available kit (Adiva Centaur System, Siemens, Germany). The intra- and inter-assay variation coefficients were 3.7-4.1% and 1.0-3.3% respectively. Fasting serum C-peptide, peak C-peptide (60 minutes) and the area under curve of the 120-minute C-peptide were measured using a mixed meal tolerance test (MMTT, as follows). Detection is performed at V1, V8, V14, V20, and V26.
- HbA1c: it was tested in local medical center laboratories independently. The measurements are performed at V1, V5, V8, V14, V20, and V26.
- MMTT: participants will be provided with instant noodles with the net weight of 75g, and without any condiment oil. Timing of the 1-hour and 2-hour postprandial tests starts from the beginning of the meal. Participants will be required to finish the meal in 15 minutes once started. Three days before the MMTT, the participants must be reminded to assure at least 150 grams of carbohydrate intake every day. Before visiting, the participants must have fasted for at least 8 hours and abstained from tobacco, alcohol and caffeine for at least 24 hours. Confirm that the patient did not take saxagliptin 3 days before visit, and did not take the insulin injection in the morning of the visit date.

### **7.2 Safety assessments**

**The following will be measured for the safety of the study**

Monitor and record all adverse events (AEs) (see study protocol 8.1) and severe adverse events (SAEs) (see study protocol 8.2), combined medications, hematology, blood biochemical and urine tests, ECG, as well as vital signs, weight, and so on.

### **7.2.1 Laboratory tests**

The sponsor will assign the central laboratory to carry out the safety assessment: test of 25(OH)D. Other clinical lab tests will be carried out at laboratories of each research center.

#### **Central laboratory test items:**

25(OH)D: using vitamin D detective kit from SIEMENS (chemiluminescence method), Detection was performed at V1, V3, V5, V8, V14, V20 and V26.

### Individual research center laboratory test items:

| type  |                          | parameter                                                                                                                                                                     |
|-------|--------------------------|-------------------------------------------------------------------------------------------------------------------------------------------------------------------------------|
| Blood | Blood routine            | Blood cell count (RBC, hemoglobin, mean corpuscular volume, leukocytes) differential blood count (neutrophils, lymphocytes, monocytes, eosinophils, basophils) and platelets. |
|       | Liver and renal function | AST, ALT, TBIL, DBIL, ALB, BUN, Cr, UA                                                                                                                                        |
|       | Lipid                    | TC, HDL-C, LDL-C, TG                                                                                                                                                          |
|       | Electrolyte              | Calcium, Phosphorus, Sodium, Potassium, Chloride, Magnesium                                                                                                                   |
|       | Others                   | HbA1c, Blood glucose                                                                                                                                                          |
| Urine | Pregnancy test           | Urine pregnancy test                                                                                                                                                          |
|       | Urine test               | 24-hour urine calcium and phosphate; UACR                                                                                                                                     |

Abbreviations: AST – aspartate transaminase, ALT – alanine transaminase, TBIL – total bilirubin, DBIL – direct bilirubin, ALB-serum albumin, BUN – blood urea nitrogen, Cr – creatinine, UA – uric acid, TC – total cholesterol, HDL-C – high density lipoprotein cholesterol, LDL-C – low density lipoprotein cholesterol, TG – triglyceride; UACR – urinary albumin-to-creatinine ratio.

Any laboratory result abnormality might meet the qualitative criteria for AE in this study (reference to 8.1.1). In these cases, all AEs related to abnormal lab results should be recorded in the CRF.

